### *Languages and translations*

The survey will be translated in the following additional languages to increase the participation and the representativity of the LGBTI communities: Arabic, Bengali, Chinese, English, Farsi, French, Gujarati, Hindi, Japanese, Marathi, Portuguese, Russian, Spanish, Thai, Turkish, Ukrainian, and Urdu.

Translations are performed from the original English version by native speakers with knowledge in the field of HIV and LGBTI. Translated documents are retranslated to English by a second translator and discrepancies are discussed with the research team and fixed.

### *Data management*

The [questionnaire](#) was transferred to an online survey tool, SurveyMonkey ensuring anonymized participation. The initial online transfer was subject to pre-testing. We recruited ten MSM through UNAIDS and community and asked them to work their way through the survey and to express what they were thinking, how the questions struck them, and any ideas that occurred as they proceeded. In response to user comments we adjusted very many small details of the survey, including correcting typographic errors; correcting routing errors; standardising the way individual questions were served; re-ordering modules; reordering flow of questions; rewording/clarification of question stems; reordering of response sets; and expansion of response sets. No questions (items) were cut in this process, although notes were made on what could be considered for the next round of the survey.

We performed a survey consultation to test and provide their feedback on the survey. Issues and question raised were considered and discussed with the consultees. The process resulted few minor changes to the survey. Following the processing of all comments, an item analysis was constructed, and discussion occurred among the core design team to identify the least essential questions while retaining as much topic balance as possible. This version of the survey was subject to an online time-trial.

The LGBT Foundation performed a small-scale test of the online survey with a random set of respondents, in order to estimate the average completion times, possible rejection through disproportionately skipped questions or attrition at a particular point in the completion of the questionnaire. This first online test went adequately and confirmed the interest of respondents in going through the complete survey. The average completion time spent on the survey is 11 minutes.

The online survey is expected to be rolled-out once received the clearance of the WHO ERC, tentatively end of April 2019. For rolling out the survey, we are aiming to establish a network with the following partners for the survey promotion on regional and national online networks:

- The LGBT Foundation Communications Office (<https://lgbt.foundation/>)
- UNAIDS Press Office (<http://www.unaids.org/en/resources/presscentre>);

- UNAIDS Office of Community Mobilisation (<http://www.unaids.org/en/ourwork/programmebranch/rightsgenderpreventioncommunitymobilizationdepartment/officecommunitymobilization>);
- UNAIDS Regional Offices (<http://www.unaids.org/en/regionscountries/regions>);
- UNAIDS Country Offices (<http://www.unaids.org/en/regionscountries/countries>).

The survey will be available online for a duration of 12 weeks (3 months). Following which, unidentified data will be provided to the investigators for quality assurance, cleaning and organisation of the database.

### ***Data analysis, use and dissemination***

We selected internet sampling for it demonstrated higher number of respondents among hard-to-reach populations, faster recruitment, lower operational cost, greater level of anonymity provided to participants. Acknowledging selection bias, we may apply techniques, e.g. prediction modelling, to correct for the bias that results from differential access to, and use of, the internet. See also section (p) limitations below.

Our cross-sectional study is observational by nature and non-interventional. It does not alter the exposure status of the consenting respondents and thus warrants minimal to no risk for the participants. We will measure the outcome and the exposures in the target population and will study their association to fulfil the study objectives.

Data collected during the survey are anonymised and will be managed in a way that protects the privacy of participants and the confidentiality of the information they provided. We will take measures to prevent the unintended collection of IP addresses.

Data will be owned by the LGBT Foundation. Data will be stored on LGBT Foundation and UNAIDS in their on-premise file storage, protected with always-on real-time firewall and antivirus. Access to the anonymised individual data folder will be password protected and restricted to authorised users, after completion of a Declaration of Confidentiality and Data Privacy. Data are not and will not be monetised. Any data shared outside the survey team – such as with a third party conducting secondary analysis – will be anonymized. When disseminating results, the data will be aggregated at a higher level to ensure that the information does not enable to suspect or reveal the identity of any individual participant or group of participants.

The team will likewise work on the econometric models to answer a first set of two research questions using a socioecological approach:

- Does the homophobic climate increase the vulnerability to HIV infection for LGBTI people?
- Are perceived social and economic inequalities correlated with the incidence of HIV in LGBTI community?

The data can also be used for academic purpose, such as doctoral or post-doctoral articles by the research team. [name] might use some of these data for a PhD thesis at Aix-Marseille University.

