# Abstract

**Background** Worldwide, lesbian, gay, bisexual, transgender and intersex (LGBTI) people contend with high risks for HIV infection, stigma and discrimination, and for exclusion from HIV and other health services. In many low- and middle-income countries, LGBTI people are often hidden, marginalised and difficult to assess as part of general population-based surveys. Thus, assessing their exposures and outcomes and burden of HIV disease is extremely challenging. This presents a dilemma for HIV surveillance as their omission from surveillance systems leaves significant gaps in our understanding of HIV epidemics.

**Objective** This research project is aimed at conducting an observational, non-interventional, global cross-sectional internet survey in LGBTI participants to examine how various demographic, economic, socioecological, homophobic, psychosocial, attitudinal and behavioural variables potentiate HIV risk behaviour. We likewise aim to examine self-reported HIV prevalence, exposure to HIV related stigma and discrimination, and to study the association between these socioecological parameters and HIV care and treatment coverage in the survey participants.

**Methods** We imply internet sampling method to conduct the cross-sectional survey recruiting consenting adult LGBTI participants. We select internet sampling for it demonstrated to be particularly useful for hard-to-sample populations, higher number of respondents among hard-to-reach populations, faster recruitment, lower operational cost, greater level of anonymity and security provided to participants. Acknowledging selection bias, we may apply techniques, e.g. prediction modelling, to correct for the bias that results from differential access to, and use of, the internet. To safeguard the data privacy, rights and welfare of the research participants, the access to the online survey will be provided via anonymous weblink. The survey will be opened for three (3) months. Our cross-sectional study is observational by nature and it does not alter the exposure status of the consenting respondents and thus warrants minimal to no risk for the participants. We will examine the outcome and the exposures in the target population and will study their association. Our survey questionnaire provides essential components to fulfil the above objective and was developed using selected standard protocols.

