## Methods and Design

### a) The scientific design of the study

#### *The survey objectives*

This research project is aimed to:

- conduct a cross-sectional observational, non-interventional, internet survey in consenting 18+ year-old LGBTI participants using an anonymous web-based self-administered questionnaire without any geographical restrictions;
- examine correlates of HIV infection to understand how survey variables, such as demographic, economic, socioecological, homophobic, psychosocial, attitudinal and behavioural, potentiate HIV risk behaviour and access to and uptake of HIV care and treatment services;
- provide evidence in favour of more LGBTI-inclusive health and HIV service delivery, advocacy, and policymaking.

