### *Timing and intervals between the survey rounds*

This is the first edition of the global LGBTI survey. Future annual edition of the survey will be determined after the evaluation of the 2019 edition. A tentative timeline for this survey can be found in appendix 3.

One interest of eventual annual editions of the survey is to study the changes and the evolution of key variables over time per country. The study does not track respondents year after year. It will analyse how indicators such as well-being, mental health, HIV self-prevention, homophobia for example are evolving following changes in LGBTI legislation, in government, or in the economy at country level.

This is similar as other surveillance. It typically does not include the same participants in repeat surveys. Ideally, behavioural surveys should be conducted at intervals in order to capture changes in risk behaviours and the HIV epidemic over time. This survey can therefore serve as a baseline for any future undertakings.

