- ☐ yes
- ☐ no
- ☐ don't know
- ☐ does not apply

*[Section on quality of sex]*

34. Over the past three months, how satisfied are you with the quality of your sexual life?

- ☐ 10 really satisfied
- ☐ 9
- ☐ 8
- ☐ 7
- ☐ 6
- ☐ 5
- ☐ 4
- ☐ 3
- ☐ 2
- ☐ 1 really not satisfied

35. I would like to have sex

- ☐ a lot more often
- ☐ a little more often
- ☐ I have enough sex as is
- ☐ a little less often
- ☐ a lot less often

*[Section on sociodemographic data]*

36. Your relationship situation

- ☐ single
- ☐ in a relationship with a man
- ☐ in a relation with a transgender person
- ☐ in a relationship with a woman
- ☐ both with a man and a woman
- ☐ I don't know

37. Education (highest degree completed):

- ☐ none
- ☐ primary school
- ☐ secondary /high school
- ☐ university first degree
- ☐ masters/doctorate

38. Current employment status:

- ☐ employed
- ☐ self-employed
- ☐ doing casual or part-time work
- ☐ unemployed
- ☐ student
- ☐ retired
- ☐ other

*[Section on economic situation]*

39. Which comes closest to your feelings about your income these days?

- ☐ living really comfortably on present income
- ☐ living comfortably on present income
- ☐ neither comfortable nor struggling on present income
- ☐ struggling on present income
- ☐ really struggling on present income

40. Considering all debts or loans of whatever type, were you behind with payments by more than 3 months at any time during the last 12 months?

- ☐ never
- ☐ rarely
- ☐ occasionally
- ☐ most of the time
- ☐ all the time
- ☐ does not apply

41. How often have there been times in your life when you have lived in poverty by the standards of that time?

- ☐ never
- ☐ rarely
- ☐ occasionally
- ☐ most of the time

*[Section on social situation]*

42. Think of a ladder representing where people stand in **your country**

At the **top** of the ladder are the people who are the **best off**. At the **bottom** are the people who are the **worst off**. Where would you place yourself on this ladder at this moment?

- ☐ 10 among those having most money, most education and

- most respected jobs
- ☐ 9
  - ☐ 8
  - ☐ 7
  - ☐ 6
  - ☐ 5
  - ☐ 4
  - ☐ 3
  - ☐ 2
  - ☐ 1 among those having the least money, least education and least respected jobs or no job

43. Now, think of a ladder representing where people stand in your **local community**

Where would you place yourself on this ladder at this moment?

- ☐ 10 highest social standing in my community
- ☐ 9
- ☐ 8
- ☐ 7
- ☐ 6
- ☐ 5
- ☐ 4
- ☐ 3
- ☐ 2

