- ☐ all of it
- ☐ does not apply to me

50. In the past 3 months, did you share drug injecting equipment (needles, syringes) with someone else?

- ☐ yes, once
- ☐ yes, several times
- ☐ no, I don't share my equipment
- ☐ no, I don't inject drugs

51. What do you do if your potential date/sexual partner tells you they are is HIV positive? (tick as many as you like)

- ☐ I do not see them again
- ☐ I am not comfortable having sex with them
- ☐ I am comfortable having sex with them because we use a condom, I am on PrEP and/or he is undetectable
- ☐ I'm HIV positive too

52. In the last 12 months, how often have **you paid someone** to have sex with you?

- ☐ never
- ☐ 1-2
- ☐ 3-10
- ☐ 11-50
- ☐ more than 50 times

53. In the last 12 months, how often have **you been paid** to have sex

- ☐ never
- ☐ 1-2
- ☐ 3-10
- ☐ 11-50
- ☐ more than 50 times

54. I feel comfortable in gay bars

- ☐ 7 strongly agree
- ☐ 6
- ☐ 5
- ☐ 4 undecided
- ☐ 3
- ☐ 2
- ☐ 1 strongly disagree
- ☐ does not apply

55. Social situations with gay men make me feel uncomfortable

- ☐ 7 strongly agree

- ☐ 6
- ☐ 5
- ☐ 4 undecided
- ☐ 3
- ☐ 2
- ☐ 1 strongly disagree
- ☐ does not apply

56. I feel comfortable being seen in public with an obviously gay person

- ☐ 7 strongly agree
- ☐ 6
- ☐ 5
- ☐ 4 undecided
- ☐ 3
- ☐ 2
- ☐ 1 strongly disagree
- ☐ does not apply

57. I feel comfortable discussing homosexuality in a public situation

- ☐ 7 strongly agree
- ☐ 6
- ☐ 5
- ☐ 4 undecided
- ☐ 3
- ☐ 2
- ☐ 1 strongly disagree
- ☐ does not apply

58. I feel comfortable being sexually attracted to other men

- ☐ 7 strongly agree
- ☐ 6
- ☐ 5
- ☐ 4 undecided
- ☐ 3
- ☐ 2
- ☐ 1 strongly disagree
- ☐ does not apply

59. Homosexuality is morally acceptable to me

- ☐ 7 strongly agree
- ☐ 6
- ☐ 5
- ☐ 4 undecided
- ☐ 3
- ☐ 2
- ☐ 1 strongly disagree
- ☐ does not apply

60. Even if I could change my sexual orientation, I wouldn't

- ☐ 7 strongly agree

- ☐ 6
- ☐ 5
- ☐ 4 undecided
- ☐ 3
- ☐ 2
- ☐ 1 strongly disagree
- ☐ does not apply

61. Do you know your HIV status?

- ☐ I'm HIV-negative
- ☐ I'm HIV-positive
- ☐ I don't know
- ☐ I don't want to answer

- ☐ PREV (*clicking here brings the respondent to earlier module in case she/he would like to change*)
- ☐ DONE (*brings the respondent to a thank you message*)

*Note: participants that have answered "I'm HIV-positive" at question will be offered to participate to module 3 (see next page)*

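### The second research question takes HIV incidence as its outcome, but the survey can only measure self-reported HIV prevalence

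*Protocol*

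**What the plan says.** Protocol, Data analysis, use and dissemination, introduces the analysis as follows: "The team will likewise work on the econometric models to answer a first set of two research questions using a socioecological approach". The second of the two questions is "Are perceived social and economic inequalities correlated with the incidence of HIV in LGBTI community".

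The rest of the protocol describes a different kind of measurement:

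- **Aim (Abstract).** "We likewise aim to examine self-reported HIV prevalence". The topic list under Questionnaire development also names HIV prevalence, and the sample size section speaks of correlates of HIV infection in the participants.
- **Design (The survey objectives).** The first objective is to "conduct a cross-sectional observational, non-interventional, internet survey in consenting 18+ year-old LGBTI participants using an anonymous web-based self-administered questionnaire".
- **Rounds and follow-up (Timing and intervals between the survey rounds).** "This is the first edition of the global LGBTI survey", later editions are undecided, and "The study does not track respondents year after year".
- **Infection status (Appendix 1, question 61).** "Do you know your HIV status", with four answers: negative, positive, not known, or prefer not to say.
- **Test timing (Appendix 1, question 29).** The time of the last HIV test in broad bands (six months, twelve months, longer ago, never). It asks for no result.
- **HIV module (Appendix 1, questions 62 to 82).** Stigma, disclosure, treatment and viral load. No item asks when HIV was acquired or diagnosed.

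**The concern.** Incidence counts new infections against time at risk. To measure it, a study needs follow-up of uninfected people, or a dated transition from negative to positive, or a marker of recent infection. None of these appears in the protocol. What question 61 yields is the proportion of respondents who say they are HIV-positive, whenever they were infected.

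Prevalence is a legitimate outcome, but it is a different one. It rises with incidence and also with survival and time since infection, and self-reported prevalence depends on who has been tested. A factor can therefore be associated with prevalence without being associated with new infection, and the reverse. There is also a problem of time order: someone diagnosed years ago may report low income or low standing today because of HIV.

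The stake is what the study will be said to have shown. Results are to go onto country dashboards and into advocacy material (Feedbacks of results to communities). Under the present wording, an association with prevalence could be published there as an association with new infections.

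**Working it through.** The protocol states no figure on this point, so the check is whether the outcome can be obtained from the data to be collected.

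**1. Routes to incidence, compared with the protocol**

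| Route | What it needs | What the protocol provides |
|---|---|---|
| Follow-up | The same people observed at least twice | One round; respondents are not tracked |
| Dated transition | Date of first positive and of last negative test | Neither is asked in questions 29, 46–53 or 61–82 |
| Recency marker | A specimen or assay | None; the survey is a web questionnaire |
| Recent diagnosis as proxy | Proof that the latest test was the first positive one | Question 29 gives only when the last test took place |
| Derivation from prevalence by age | A representative sample and strong assumptions | The sample size section disclaims representativeness |
| External incidence figures | A named source | None named |

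The fourth row needs care, because question 29 crossed with question 61 is the closest the questionnaire comes. A positive respondent tested in the last six months may have been diagnosed at that test or many years before it. No earlier negative result is recorded, and a diagnosis date is not an infection date. The cross-tabulation does not isolate new infections.

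**2. Is the word used loosely elsewhere?** Section b) on relevance mentions incidence alongside new infections when describing the global epidemic. That is the ordinary meaning, applied to background epidemiology. It supplies no survey outcome.

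**3. Why prevalence cannot stand in for incidence.** In a steady state, with prevalence P, incidence I and mean duration D,

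P / (1 − P) = I × D.

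The values below are assumptions chosen for illustration. None comes from the protocol.

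- I = 1% per year, D = 30 years: odds = 0.01 × 30 = 0.30, so P = 0.30 / 1.30 = 23.1%.
- I = 2% per year, D = 15 years: odds = 0.02 × 15 = 0.30, so P = 23.1%.
- I = 1% per year, D = 10 years: odds = 0.01 × 10 = 0.10, so P = 0.10 / 1.10 = 9.1%.

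The first two groups have the same prevalence and a two-fold difference in incidence. The first and third have the same incidence and different prevalences. Prevalence alone does not identify incidence, whichever values are chosen.

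**4. Time order.** Several items on economic and social position refer to the present. Question 39, for example, asks "Which comes closest to your feelings about your income these days", and the ladders in questions 42 and 43 ask for standing at the time of answering. For a positive respondent these follow infection by an unknown interval.

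**5. Is this already acknowledged?** Section p) lists representativity, internet access, differences between languages, and self-report that cannot be verified. It does not mention prevalence against incidence, or reverse causation.

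**The case against.** The best defence is that this is one wrong word. The Abstract, the topic list and the sample size section all name outcomes the survey can measure, and sampling, sample size and data collection stay the same once the word is corrected. That is true, and it is why the fix is small. It does not remove the point, because the word defines the outcome of one of only two named research questions. An analysis plan could not repair it either, since the data needed for incidence are not collected.

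Several stronger readings are tempting, and the protocol does not support them:

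- **That the question makes a causal claim.** It asks about correlation, and the same section speaks of studying association. The fault lies in the outcome.
- **That question 61 is the only HIV outcome.** It is the only infection-status item. The questionnaire also covers testing (question 29), sex without any prevention method (questions 46–48), shared injecting equipment (question 50), treatment (question 80) and viral suppression (question 81).
- **That questions 39, 42 and 43 are the designated exposures.** No section assigns items to this research question. Questions 33, 40 and 41 are equally plausible.
- **That education (question 37) and lifetime poverty (question 41) should become the main exposures.** The question concerns perceived inequalities, which the ladders address directly, whereas attained education does not. Question 41 also covers time after infection, so it does not remove reverse causation.
- **That the resulting error can be put at 50% to 100%.** This follows only if duration is assumed to differ 1.5- to 2-fold between groups. The documents give no such figure, and the steady-state formula is a poor model for a self-selected web sample.

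**Conclusion.** The outcome of the second research question is wrongly stated. A single untracked cross-sectional survey with one current-status item and no test dates cannot measure HIV incidence, and the wording contradicts the protocol's own prevalence aim. This conclusion rests on the protocol text alone and needs no numerical assumption. The steady-state figures only illustrate why the two quantities differ.

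The scope is one of the two named research questions. The size of the error, if prevalence results were reported as incidence, cannot be estimated from the documents, and neither can its direction. A reader might infer that the design has failed or that the questionnaire must be extended. Neither follows: the survey can address the question once it is restated for prevalence.

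**What to change.** 1. In Data analysis, use and dissemination, replace the outcome of the second question with *self-reported HIV prevalence among respondents who report knowing their status*. In terms of question 61, the denominator is those answering negative or positive.
2. In section p), add that prevalence also reflects survival, time since infection and testing. Add that perceived income and social standing measured now (for example questions 39, 42 and 43) may be consequences of HIV. State that results will therefore not be reported as incidence or as risk of new infection.

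The cost is a few sentences and a less ambitious claim. Sampling, sample size and questionnaire stay as they are. An added item on the date of first positive test is not needed for this correction. It would bring translation and back-translation into the listed languages and would sit uneasily with the protocol's principle of a short questionnaire.
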